# Effect of NEuroplasticity-Principles-based SEnsory-Rehabilitation (NEPSER) on sensori-motor recovery in stroke: study protocol for a randomized controlled trial

**DOI:** 10.1186/s42466-021-00108-1

**Published:** 2021-02-04

**Keywords:** Cerebrovascular accident, Fugl-Meyer, Hand, Proprioception, Somatosensory, Stereognosis

## Abstract

**Introduction:**

Up to 2/3rd of the stroke subjects may experience impairment in any of the somatosensory modalities such as light touch, proprioception, and stereognosis. The sensory recovery is strongly associated with the level of motor recovery. Very negligible sensory-based interventions have been developed and found to be evident in enhancing the sensory deficit and associated motor recovery. The possible factor for the ineffectiveness of these sensory interventions could be lack of the neuroscientific basis in formulation of the program. Thus, the objective of the study is to determine the effectiveness of a neuralplasticity-principles-based sensory-rehabilitation protocol on motor and sensory recovery, and disability of the post-stroke hemiparetic subjects.

**Methods:**

We propose to recruit 122 poststroke subjects in a randomized controlled, assessor blinded trial to be conducted in a rehabilitation-institute. The key eligibility criteria is age between 20 to 80 years, hemiparesis (right or left), ischemic or hemorrhagic stroke, 1 to 12 months poststroke, and impairment in any of the sensory modalities. The participants in the experimental group will receive **NE**uroplasticity-**P**rinciples-based **SE**nsory-**R**ehabilitation (**NEPSER**) protocol comprising active, repetitive, and meaningful training of the specific sensory modalities utilizing visuo-perceptual, cognitive, motor, and functional tasks will be imparted for 8 weeks, 5 sessions / week, each of 2 h. The control subjects will undergo only standard rehabilitation based on neurophysiological, biomechanical, and rehabilitative approaches. All the participants will be assessed for motor (Fugl-Meyer assessment, upper extremity section) and sensory recovery [Nottingham Sensory assessment (Erasmus MC modification of the revised version)] at baseline, 8-week, and 12-week follow-up. The Semmes weinstein monofilament, two-point discrimination test and modified rankin scale (disability) will be applied as secondary measures. A repeated-measures 2-way ANOVA will be used to estimate difference for the post intervention and follow-up scores between the groups.

**Perspective:**

The proposed study will lead to development of a novel rehabilitation protocol that will not only enhance the sensory recovery but also the motor and functional recovery. This may reduce the impact of stroke disability and enhance the quality of life.

**Trial registration:**

The trial has been registered under Clinical Trial Registry of India (CTRI) as CTRI/2019/09/021442 on 30th September 2019.

## Introduction

In stroke, motor paresis being a major manifestation, has always been emphasized upon. However, subtle somatosensory impairments such as reduced ability of light touch, proprioception, stereognosis, and 2-point discrimination may also be exhibited among the poststroke subjects. Up to 2/3rd of the stroke subjects may experience impairment in any of the somatosensory modalities [1, 2].

The sensory deficits hamper the ability to utilize the available motor level in the functional tasks. The sensory recovery has been found to be strongly associated with the level of motor recovery. The impaired sensation along with the complex motor deficits increases the disability manifold. For instance, an individual with diminished light touch in hand despite good finger control may not be able to manipulate an object for functional performance. The sensory impairment is also associated with the participation restriction leading to poor quality of life [3]. Thus, integration of sensory abilities is crucial for the motor recovery.

In poststroke, sensory training of varied range has been investigated [4, 5]. The techniques may range from passive techniques such as somatosensory electrical stimulation to active retraining of stereognosis, proprioception, discriminating and localizing sensations However, most of them have not exhibited sufficient evidence for their effectiveness. Additionally, most of these techniques were not utilizing the theoretical foundation of neuroplasticity. Very few studies utilized the sensori-motor training, fulfilling some of the principles of neuroplasticity. Diego et al (2013) [6] investigated the effect of sensorimotor therapy in form of constraint induced movement therapy on chronic stroke. The construct of program had components of passive motor therapy, proprioception and touch inputs along with functional training. However, the chronic subjects of 4 to 5 years and only 16 h of therapeutic sessions were not favourable for the biological recovery [7]. Carey et al (2011) [8] conducted a randomized controlled trial by providing somatosensory discrimination training for texture and object recognition, and proprioception. The investigation exhibited favourable change for sensory recovery. However, the duration was only for 10 h with a low frequency of 3 h/week as well as the impact on the motor recovery was not examined.

In relation to stroke rehabilitation, task-specificity, environment, repetition, frequency, intensity, and meaningfulness of movements or activities are some of the evident neuroplastic principles [7]. Sensory rehabilitation protocols utilizing majority of these principles are sparse. Thus, there is a need for development and testing of a novel sensory rehabilitation regime based on the concepts of neural-reorganization.

## Methods

### Aim of the trial

The initial objective of the proposed study was to develop a sensory-deficit specific rehabilitation intervention considering the motor level of the stroke subject. The development and feasibility of the protocol has been achieved. The subsequent aim is to determine the effectiveness of the protocol on motor and sensory recovery of the upper limb among the poststroke hemiparetic participants. The research question, how the sensory deficit of the upper limb interacts with the motor-recovery process and motor therapy will be explored. The sensory deficits for the upper limb or hand such as light touch, pressure, proprioception, and stereognosis will be focussed. The substantial frequency and intensity of intervention, stage- and chronicity-specific program will be the other key aspects in the intervention regime. The motor recovery in terms of voluntary motor control for the upper limb, wrist and hand will be evaluated. Further, the overall disability status of the subjects will also be assessed. The ultimate aim of this trial is to systematically integrate sensory intervention into the motor rehabilitation of the stroke subjects in order to enhance substantial motor recovery.

### Study description and study design

#### Design

Randomized controlled, assessor blinded trial.

#### Sample size

The power calculation has been conducted using the values for motor and sensory assessment from the two different studies [9, 10]. Considering the beta = 0.1 and α = 0.05, the calculation inferred that 53 subjects in each group would be sufficient to detect the desired change. However, to compensate possible drop outs (15%), 61 subjects in each group will be enrolled. Thus, the total sample size for the proposed investigation will be 122.

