#### Allocation

The subjects will be randomly allocated between the experimental and control groups in a block of 10. The randomization process will be conducted by an office staff, not associated with the study, using the SPSS Version 23 software. The intervention will be allocated in the ratio of 1:1. The assignment will be serially arranged in the coded digital files. The principal investigator ([name]) will enroll the potential participants and assign them into the respective group. The assessor will be unaware about the group allocation of the subjects.

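### Enrolling 61 per group does not keep 53 after the stated 15% dropout; it covers about 13%, and 15% would need 63 per group

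*Protocol article*

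**What the plan says.** The Sample size section of the protocol article sets the error rates ("Considering the beta = 0.1 and α = 0.05") and reports that "the calculation inferred that 53 subjects in each group would be sufficient to detect the desired change". It adds an allowance for attrition: "However, to compensate possible drop outs (15%), 61 subjects in each group will be enrolled". The section closes with a total: "the total sample size for the proposed investigation will be 122". The Methods part of the abstract repeats the total ("We propose to recruit 122 poststroke subjects"), and the Allocation section confirms equal groups: "The intervention will be allocated in the ratio of 1:1".

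No formula is given for the step from 53 to 61. The Statistical methods section plans an intention-to-treat analysis in which missing values are filled by carrying the last observation forward.

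**The concern.** Dropouts are lost from the people enrolled, so an allowance of 15% has to be applied to the enrolled number. The required number is divided by 0.85. Multiplying it by 1.15 gives a smaller answer, and the gap between the two widens as the dropout rate rises.

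If the smaller answer was used, a trial that loses exactly the share it planned for ends with fewer subjects than it calls sufficient. The stated beta of 0.1 is then not quite met at the stated dropout rate. Readers will also judge the observed attrition against a 15% margin that the enrolment figure does not provide.

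**Working it through.** **Inputs**, all from the Sample size section except the last:

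- required per group: 53
- dropout allowance: 15%
- enrolled per group: 61; total 122
- α = 0.05 (one- or two-sided not stated); β = 0.1, so power 90%
- allocation 1:1 (Allocation section)

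**1. Reproducing the plan's figure.** Required × (1 + dropout) = 53 × 1.15 = 60.95, rounded up to 61. Doubled, this is 122. Both match the article exactly. Because no formula is printed, the multiplication is an inference from this match.

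**2. What 61 leaves after 15% loss.** Enrolled × (1 − dropout) = 61 × 0.85 = 51.85 per group, or 122 × 0.85 = 103.7 in total. The requirement is 53 per group, 106 in total. This step does not depend on how 61 was reached.

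**3. What keeps 53 after 15% loss.** Required / (1 − dropout) = 53/0.85 = 62.35, rounded up to 63 per group, or 126 in total. Check: 63 × 0.85 = 53.55, which meets 53, whereas 62 × 0.85 = 52.70 does not. If only the total is inflated, 106/0.85 = 124.7, or 125.

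**4. What loss 61 can absorb.** (61 − 53)/61 = 8/61 = 13.1%.

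**5. Effect on power.** The article gives no effect size or SD, so I took the standardised difference that yields 90% power at 53 per group and held it fixed. This assumes an unadjusted comparison of two means. In the normal approximation the difference is d = (z for α + z for power) × √(2/53).

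| Assumed test | d giving 90% at 53 | Power at 51 | Power at 52 | Power at 53 |
|---|---|---|---|---|
| Two-sided t test | 0.636 | 88.9% | 89.4% | 90.0% |
| Two-sided, normal approximation | 0.630 | 88.9% | 89.5% | 90.0% |
| One-sided, normal approximation | 0.568 | 89.0% | 89.5% | 90.0% |

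The loss is 0.5 to 1.1 percentage points, whichever version is used.

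**The case against.** Four points can be made for the plan.

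*The 15% may mean 15% of 53.* On that reading the sum closes: 53 + 8 = 61, and twice 61 is 122. But a dropout rate is ordinarily a share of participants, and the section does not define it otherwise. On this reading the trial still tolerates only 13.1% of those enrolled, so the sentence would need clarifying anyway.

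*Carrying the last observation forward keeps all 61 per group in the analysis.* This is true of the count, and it means that the power figures above are not those of the planned analysis. It does not rescue the allowance. A carried-forward value is not an observed 8-week or 12-week outcome, and the Sample size section itself treats dropouts as a loss to be made good by extra enrolment.

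*The gap is smaller than other unknowns.* The Statistical methods section uses the pre-intervention score as a covariate. If 53 came from an unadjusted calculation, which is not stated, a correlation between baseline and outcome of about 0.15 would offset the loss: 1 − r² = 51.85/53 = 0.978, so r = √0.022 ≈ 0.15. This is a fair argument that the consequence is slight. It is not an argument that the stated figure is right.

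*The formula is inferred.* It is, but the shortfall in step 2 needs no formula.

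What stands is that the effect is minor, and that any statement about power rests on assumptions which the article does not let a reader check.

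**Conclusion.** The error is real and small. As printed, 53, 15% and 61 are inconsistent: 61 per group is 2 short of the 63 needed (4 short in total), and 15% loss leaves 51 to 52 per group instead of 53. This part rests only on the article's own numbers and on reading the dropout rate as a share of those enrolled.

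The power figure of about 89% rests further on 53 giving exactly 90% in an unadjusted two-group comparison of observed outcomes. The base figure of 53 cannot be verified from the article and is taken as given. The shortfall does not threaten the trial's ability to answer its question, but the sample-size statement should be corrected.

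**What to change.** Keep 122 and restate the allowance: 61 per group retains 53 with observed outcomes if dropout does not exceed about 13% (8/61). This costs one sentence and a slightly less favourable stated margin. It changes nothing in the design, conduct or analysis.

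The sponsor could instead keep the 15% and state that power at that loss is about 89%, but only with the effect size, SD and test behind the 53 given alongside.

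If the 15% allowance and the 90% power are both to be kept, the target is 63 per group, 126 in total. That means 4 more subjects, and the total in the abstract must change with it.

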#### Allocation

The subjects will be randomly allocated between the experimental and control groups in a block of 10. The randomization process will be conducted by an office staff, not associated with the study, using the SPSS Version 23 software. The intervention will be allocated in the ratio of 1:1. The assignment will be serially arranged in the coded digital files. The principal investigator ([name]) will enroll the potential participants and assign them into the respective group. The assessor will be unaware about the group allocation of the subjects.

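### The investigator who enrols also assigns, in a single block size of 10, so the person deciding entry can partly predict the next allocation

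*Protocol article*

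**What the plan says.** The Design section describes the trial as "Randomized controlled, assessor blinded trial". The Allocation section then sets out the procedure:

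- Participants are "randomly allocated between the experimental and control groups in a block of 10", and "The intervention will be allocated in the ratio of 1:1". One block size is given, and no stratification is mentioned.
- "The randomization process will be conducted by an office staff, not associated with the study".
- "The assignment will be serially arranged in the coded digital files". The article does not say who holds these files or what the coding hides.
- The principal investigator "will enroll the potential participants and assign them into the respective group".
- "The assessor will be unaware about the group allocation of the subjects". No one else is described as unaware of allocation.

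Other sections set the context. The Abstract places the trial in a rehabilitation institute. The arms differ visibly: sensory training in one, mainly motor tasks in the other. Eligibility spans FMA-UE 0 to 66 and 1 to 12 months after stroke. Statistical methods names the pre-intervention score as the only covariate. Perspective has recruitment running from October 2019 to an expected end in July 2022; the article appeared in February 2021.

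**The concern.** Independent generation of a sequence is not the same as concealing it. Here the person who judges eligibility and decides when a patient enters also makes every assignment, and so knows the allocation of everyone enrolled so far. With one block size, a 1:1 ratio and no stratification described, a single running tally shows which arm has more places left in the current block and, towards its end, sometimes which arm must come next.

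A person with that knowledge can include, decline or delay the next candidate, consciously or not. Some criteria leave room for judgement, such as the ability to comprehend instructions or severe cognitive deficit assessed partly by clinical tests. Prognosis is likely to vary widely over the range of motor scores and times since stroke admitted. If entry were steered, the arms would differ in prognosis before treatment began. Blinding the assessor protects measurement of the outcome, not the decision to enrol.

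**Working it through.** **The plan's own total.** Sample size gives 53 per group and 15% for drop-outs: 53 × 1.15 = 60.95, rounded up to 61, so 2 × 61 = 122. With blocks of 10, 122/10 = 12.2: 12 full blocks (120 participants) plus 2 participants in a thirteenth. This total serves only to count blocks.

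**Inputs.** Block size 2m = 10, so m = 5 places per arm (Allocation). Assumptions: the block size never varies, which is the natural reading of the text; the investigator knows it and keeps count; and the files hide the next entry until it is opened, which is the favourable reading.

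**Allocations known with certainty.** An allocation is certain once one arm has used its 5 places. The expected number of places of one arm that fall after the last place of the other is m/(m + 1). Adding both arms:

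2m/(m + 1) = 10/6 = 1.67 per block, or 16.7%.

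Over 12 blocks: 12 × 10/6 = 20. The first two places of a block are never certain, so the total stays at 20 of 122 (16.4%).

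**Correct guesses.** The best strategy is to name the arm with more places left, and to toss a coin when they are equal. Expected correct guesses per block:

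m + 2^(2m−1)/C(2m, m) − 1/2 = 5 + 512/252 − 0.5 = 6.53 of 10, or 65.3%.

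Over 12 blocks this is 12 × 6.532 = 78.4 of 120. The two participants in the last block add 0.5 + 5/9 = 1.06, giving 79.4 of 122, or 65.1%. Full concealment gives 50%. An exact recursion over the 5 + 5 block returns the same 1.67 and 6.53.

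**Would varying the block size be enough?** Simulation of 1,500 trials of 122 participants, with an investigator who still assigns and knows which sizes are possible (sizes illustrative):

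| Scheme | Certain | Best guess correct |
|---|---|---|
| Always 10 | 16.5% | 65.1% |
| Random 4, 6, 8 | 2.3% | 67.9% |
| Random 6, 8, 10 | 1.6% | 66.3% |

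Varying the size removes most of the certain allocations but does not reduce guessing. If the enroller does not know past allocations and each new one is released independently after enrolment is fixed, none is certain and guessing returns to 50%.

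**The case against.** The strongest case on the other side has four parts.

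- **The figures describe opportunity, not bias.** About 5 in 6 allocations are not certain even to someone who keeps count, and 10 is among the less predictable block sizes: by the same recursion, a constant block of 4 makes 33.3% certain with 70.8% guessed correctly. This stands. Prediction is partial, and nothing in the article shows steering or allows its effect on the outcome to be estimated.
- **The article condenses a fuller protocol.** Custody of the files and the order of release may be set out there, and coding may mask each entry until it is opened. This also stands. A reader might infer from the serial arrangement that the investigator can look ahead and see every upcoming allocation. The text does not support that: it calls the files coded and names no custodian. The calculation above does not use it; it needs only the stated facts that one person enrols and assigns, with one block size.
- **The analysis adjusts for baseline.** Statistical methods takes the pre-intervention score as covariate, so steering on a visible baseline FMA or sensory score would be largely absorbed. This stands and narrows the consequence. It does not cover time since stroke, which is not a listed covariate, or unmeasured prognosis such as motivation or expected adherence.
- **The remedy may leave guessing unchanged.** On one site with visibly different treatments, an enroller may still learn past allocations. This is a fair limit, and it is why varied blocks cannot be the main remedy.

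**Conclusion.** The point holds as a moderate design weakness that should be corrected. By stated procedure, the person deciding entry knows the past allocations, and with a single block size of 10 at 1:1 can be certain of about 20 of 122 and guess about 65% correctly instead of 50%. This rests on a constant block size and on an investigator who knows it and keeps count; it does not rest on sight of unopened entries.

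It should not be read as saying that allocations in general are predictable, or that selection has occurred. The exposure that remains after the planned covariate adjustment is selection on time since stroke and on unmeasured prognosis. Assessor blinding does not touch it.

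**What to change.** For participants not yet enrolled:

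1. The office staff who are not associated with the study hold the list and release one allocation at a time, only after consent, eligibility and baseline assessment are irrevocably recorded.
2. The Allocation section no longer gives assignment to the principal investigator, whose role ends at enrolment.
3. The enroller is kept unaware of past allocations where feasible. This matters because release after recording stops a disclosed allocation from changing that participant's entry, but does not stop someone who knows the earlier arms from guessing the next.
4. As a supplement, from the next block on, the office staff use randomly varying block sizes that are not disclosed to the study team. This cuts the certain allocations and should not be presented as lowering the guess rate.

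The cost is a protocol amendment, a documented decision on the partly used block, and a short wait at each enrolment. The staff are already involved, and no treatment, outcome or sample size changes.

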#### Participant timelines

The timeline for schedule of enrolment, interventions, and assessment as per SPIRIT guidelines is provided in Fig. 1*.*

**Fig. 1 Fig1:**
[figure not shown]
Timeline for schedule of enrolment, interventions, and assessment as per SPIRIT guidelines. -t1 = prior to enrolment, t1 = baseline assessment, t2 = assessment after 8 weeks of intervention, t3 = assessment after four-week follow-up (12 weeks after start of intervention). FMA = Fugl-Meyer assessment, Em-NSA = Erasmus MC modification of the revised Nottingham Sensory Assessment, NSA = Nottingham Sensory Assessment, SWM = Semmes-Weinstein monofilaments, 2-PD = Two-point discrimination, mRS = modified Rankin scale. NEPSER = **NE**uroplasticity-**P**rinciples-based **SE**nsory-**R**ehabilitation

### Eligibility criteria

The subjects will be recruited if they exhibit the following key criteria: 1) Age - 20 to 80 years, 2) Hemiparesis (right or left) (as assessed by Fugl-Meyer assessment [11] upper extremity subsection: 0 to 66), 3) First episode of unilateral stroke, 4) Ischemic or hemorrhagic stroke, 5) 1 to 12 months after the stroke onset, 6) Impaired or more sensory deficit of any of the sensory modalities (< 7/8) [1] as discerned by Nottingham Sensory Assessment (Erasmus MC modification of the revised version) [12], and 6) Able to comprehend instructions and perceive assessments. However, the participants will be excluded if they demonstrate any of the following: 1) Receptive communication or other language disorder (which could interfere with the assessment and treatment process), 2) Contractures and deformities of hand / finger, 3) Complex regional pain syndrome, 4) Severe cognitive or perceptual deficit (as evaluated by the National Institutes of Health Stroke Subscales [13] and clinical tests: copying and drawing, line-bisection, cancellation tasks, and functional performance), 5) Diabetic or any other neuropathy, 6) Skin disorder, and 7) Peripheral nerve injury of either of the upper limbs.

